[figure not shown]

## LIST OF ABBREVIATIONS

|                           |                                                                                                                                      |
|---------------------------|--------------------------------------------------------------------------------------------------------------------------------------|
| AGC                | Atypical glandular cells                                                                                                             |
| Al(OH)3 | Aluminum hydroxide                                                                                                                   |
| AS04               | GlaxoSmithKline's proprietary adjuvant system consisting of aluminium salt plus 3- O -desacyl-4'-monophosphoryl lipid A (MPL) |
| ASC-H              | Atypical squamous cells, cannot exclude HSIL                                                                                         |
| ASC-US             | Atypical squamous cells of undetermined significance                                                                                 |
| ATP                | According-to-protocol (or protocol defined)                                                                                          |
| CI                 | Confidence Interval                                                                                                                  |
| CIN                | Cervical intraepithelial neoplasia                                                                                                   |
| CIN1               | Cervical intraepithelial neoplasia as CIN1 adenocarcinoma in-situ and invasive cervical cancer                                       |
| CIN2+              | Cervical intraepithelial neoplasia as CIN2, CIN3 adenocarcinoma in-situ and invasive cervical cancer                                 |
| CRF                | Case Report Form                                                                                                                     |
| DNA                | Deoxyribonucleic acid                                                                                                                |
| ELISA              | Enzyme-linked immunosorbent assay                                                                                                    |
| GSK                | GlaxoSmithKline                                                                                                                      |
| HAV                | Hepatitis A virus                                                                                                                    |
| HPV                | Human papillomavirus                                                                                                                 |
| HSIL               | High grade squamous intraepithelial lesion                                                                                           |
| LBC                | Liquid Based Cytology                                                                                                                |
| LSIL               | Low grade squamous intraepithelial lesion                                                                                            |
| MPL®               | 3-deacylated monophosphoryl lipid A                                                                                                  |
| PCR                | Polymerase chain reaction                                                                                                            |
| SAP                | Statistical analysis plan                                                                                                            |
| SBIR               | Simply the Best Internet Randomization                                                                                               |
| TAA                | Type assignment algorithm                                                                                                            |
| TVC                | Total vaccinated cohort                                                                                                              |
| TVC-Control arm    | Total vaccinated cohort for control arm                                                                                              |
| TVC-1              | Total vaccinated cohort for efficacy 1                                                                                               |
| TVC-1-Control arm  | Total vaccinated cohort 1 for control arm                                                                                            |
| VLP                | Virus-like particle                                                                                                                  |

# 1 CONTEXT OF THE RAP DEVELOPMENT

This statistical analysis plan (SAP) describes the epidemiological approach used to investigate the progression from an initial cervical HPV infection to cervical pre-cancer and cancer. As most HPV infections are cleared by the immune system and do not result in clinical complications such as cervical pre-cancer and cancer, the clearance of HPV infections will be also investigated. In addition, the time to first HPV infection and to first persistent HPV infection will be explored.

Thus, the study objectives are to describe the following outcomes:

- i) the time between confirmed persistent cervical HPV infections and the development of CIN associated with the same HPV type,
- ii) the time between any cervical HPV infections and the development of CIN associated with the same HPV type,
- iii) the clearance of cervical HPV infections,
- iv) the time between the start of sexual activity and a first incident or a first persistent cervical HPV infection,

and to assess the effect on these outcomes of determinants such as sexual behavior, smoking history etc. known to predispose subjects to cervical HPV infections and/or clinical complications of HPV infections such as pre-cancer and cervical cancer.

The analyses will be performed using data obtained from the subjects included in the control arm of the HPV-008 study (End-of-Study (M48) database from the Phase III pivotal study to evaluate the efficacy of HPV-16/18 VLP AS04 vaccine compared with control HAV vaccine).

More specifically, analyses will include the use of the following data collected at enrolment and during all the visits over the 48-month follow-up of the control arm subjects included in the HPV-008 study:

- i) virological (cervical HPV infection detected by PCR in cervical liquid-based cytology (LBC) samples),
- ii) cyto-pathological examinations on LBC samples and histology samples (colposcopy performed according to the clinical management algorithms defined for the HPV-008 study),
- iii) HPV-16/18 serostatus (by ELISA) at enrolment,
- iv) socio-demographic and behavioral data.

Of note, the results of the analysis of the time between the start of sexual activity and a first incident or a first persistent cervical HPV infection will be presented in a stand-alone statistical report.

## 2 DETAILED PLAN OF ANALYSES

### 2.1 Primary objective

- To describe and evaluate the effect of clinical and behavioral determinants on the time between onset of **confirmed 6-month persistent cervical HPV infections** and detection of histopathologically-confirmed **CIN2+** associated with the same HPV type.

### 2.2 Secondary objectives

- To describe and evaluate the effect of clinical and behavioral determinants on the time between onset of **confirmed 6-month persistent cervical HPV infections** and detection of histopathologically-confirmed **CIN1+** associated with the same HPV type,
- To describe and evaluate the effect of clinical and behavioral determinants on the time between onset of **confirmed 6-month persistent cervical HPV infections** and detection of histopathologically-confirmed **CIN3+** associated with the same HPV type,
- To describe and evaluate the effect of clinical and behavioral determinants on the time between onset of **any cervical HPV infections** and detection of histopathologically-confirmed **CIN2+** associated with the same HPV type,
- To describe and evaluate the effect of clinical and behavioral determinants on the time between onset of **any cervical HPV infections** and detection of histopathologically-confirmed **CIN1+** associated with the same HPV type,
- To describe and evaluate the effect of clinical and behavioral determinants on the time between onset of **any cervical HPV infections** and detection of histopathologically-confirmed **CIN3+** associated with the same HPV type,
- To describe and evaluate the effect of clinical and behavioral determinants on the **clearance of cervical HPV infections**,
- To describe and evaluate the effect of clinical and behavioral determinants on the time between the **start of sexual activity** and **first detected incident cervical HPV infection**,
- To described and evaluate the effect of clinical and behavioral determinants on the time between the **start of sexual activity** and onset of **first confirmed 6-month persistent cervical HPV infection**.

The term “detected infection” is used instead of “new infection” as it is not possible to differentiate newly acquired cervical HPV infections from reactivation of previously acquired cervical HPV infections.

### 3 HPV-008 DATA TO BE USED FOR ANALYSES

#### 3.1 Summary of the HPV-008 study design

This section describes the overall design of this HPV-008 efficacy trial. Please refer to the following documents for more details:

- Clinical study report (Development Phase III – BB-IND 7920) for the HPV-008 study dated February 2009,
- Amended final CSR dated May 2010,
- End-of-study report (Month 48).

**Figure 1 Study Overview**

[figure not shown]

- **Experimental design:** A phase III, controlled, multi-center (n=135), and multi-country (n=14) study with two parallel groups.
- **Treatment Groups:** 2 groups: vaccine and control
  - Vaccine: 20µg HPV-16 L1 VLP/20µg and HPV-18 L1 VLP/50µg MPL®/ 500µg aluminum in the form of Al(OH)3,
  - Control: Hepatitis A vaccine (Havrix™-based investigational formulation) (720 ELISA units of antigen; 500µg aluminum in the form of Al(OH)3).
- **Treatment allocation:** Randomized (1:1).

- **Randomization method:** SBIR (Internet randomization).
- **Blinding:** Double-blind.
- **Enrolment period:** May 2004 to June 2005.
- **Study regions:** Asia Pacific, Europe, Latin America and North America.
- **Enrolled:** 18729 subjects aged 15-25 years. Total Vaccinated Cohort (TVC): 18644 subjects. Total Vaccinated Cohort for efficacy 1 (TVC-1): 18525 subjects.
- **Control arm** (HAV vaccine group): TVC: 9325 subjects. TVC-1: 9267 subjects.
- **Vaccination schedule(s):** Three doses of HPV vaccine or HAV vaccine (control arm) administered on a Month 0, 1, 6 schedule.
- **Study visits:** 10 study visits per subject scheduled at Months 0, 1, 6, 7, 12, 18, 24, 30, 36 and 48.
- **Total duration of the study:** 48 months of follow-up from study entry planned for all subjects.
- **Database freeze for the final analysis:** October 2008; **Database freeze for the M48 analysis:** March 2010.

### 3.2 Study procedures resulting in data to be used for analyses

- Blood samples for all subjects were drawn at Months 0, 7 and 24 and in a subset of subjects from selected study sites.
- Gynecological examinations were performed at Months 0, 12, 24, 36 and 48.
- Cervical liquid-based cytology samples were collected at Months 0, 6, 12, 18, 24, 30, 36 and 48:
  - HPV DNA typing by PCR was performed on cervical liquid-based cytology samples at Months 0, 6, 12, 18, 24, 30, 36 and 48,
  - Cytopathological examinations were performed on liquid-based cytology samples to detect abnormal cells at Months 0, 12, 24, 36 and 48 in all subjects,
  - Screening for *Chlamydia trachomatis* and *Neisseria gonorrhoeae* on liquid-based cytology samples at Months 0, 12, 24, 36 and 48.

Note: As of Protocol Amendment 2, screening for *Neisseria gonorrhoeae* was done only if considered appropriate by the investigator.

- Colposcopic referral according to appropriate clinical management algorithms. A central laboratory processed and interpreted results from liquid-based cytology and histology samples. All CIN endpoints were confirmed by an expert histopathology review panel that was blinded to vaccine status, HPV DNA status before biopsy and cytology reports. An Endpoint Committee was responsible for reviewing all available clinical and laboratory data prior to study unblinding by the external statistician to make final case assignments for all subjects assumed to meet criteria for primary and secondary efficacy endpoints.

- Behavioral questionnaire completed by interview for all subjects at Months 1, 12, 24, 36 and 48. The behavioral questionnaire (self-administered) collected specific socio-demographic and behavioral data concerning determinants that are recognized to predispose subjects to cervical HPV infection or are recognized co-factors for cervical carcinogenesis. The baseline questionnaire assessed at Month 1 collected data which occurred during past history and during the previous year. Questionnaires assessed at Month 12, 24, 36 and 48 collected data assessed during the previous year.

## 4 DATA EVALUATION

### 4.1 Endpoints

#### 4.1.1 Primary endpoint

- Histopathologically-confirmed **CIN2+** associated with the same HPV type as a previous confirmed **persistent cervical HPV infection (6-month definition)**.

#### 4.1.2 Secondary endpoints

- Histopathologically-confirmed **CIN1+** associated with the same HPV type as a previous **confirmed persistent cervical HPV infection (6-month definition)**.
- Histopathologically-confirmed **CIN3+** associated with the same HPV type as a previous **confirmed persistent cervical HPV infection (6-month definition)**.
- Histopathologically-confirmed **CIN2+** associated with the same HPV type as a previous cervical HPV infection (**any cervical HPV infection**).
- Histopathologically-confirmed **CIN1+** associated with the same HPV type as a previous cervical HPV infection (**any cervical HPV infection**).
- Histopathologically-confirmed **CIN3+** associated with the same HPV type as a previous cervical HPV infection (**any cervical HPV infection**).
- **Clearance** of cervical HPV infections,
- **First detected incident cervical HPV infection** following the start of sexual activity,
- **First confirmed persistent cervical HPV infection (6-month definition)** following the start of sexual activity.

The case definitions associated with the endpoints (i.e. for the determination of incident, transient, persistent and other cervical HPV infections and histopathologically-confirmed CIN associated with a given HPV type) can be found in Sections 4.3.1 and 4.3.2.

### 4.2 Study cohorts

The Total vaccinated cohort 1 for Control arm (TVC-1-Control arm) will be used for the analyses. The TVC-1-Control arm will include all vaccinated subjects (i.e. who received at

least one vaccine dose), who were randomized to the control arm of HPV-008 study, for whom data are available for analysis of endpoints and who have a normal or low-grade cytology (i.e. negative or ASC-US or LSIL) at Month 0.

In previous analyses using the TVC-1-Control arm, subjects also had to be negative for HPV DNA (by PCR) at Month 0 for the corresponding HPV type in the analysis (i.e. HPV type associated with the endpoint). In the current statistical analysis plan, some of the analyses performed on subjects from the TVC-1-Control arm will take into account subjects who tested positive for HPV DNA at Month 0 or for whom PCR result is not available at Month 0.

A flowchart of the study cohorts can be found in Section 8.1.

### 4.3 Case definitions associated with endpoints

Incident, transient, persistent and other cervical HPV infections as well as histopathological endpoints will be defined according to the rules described in both the HPV-008 study protocol and the RAP for efficacy analyses (Amendment 2 dated 8 August 2008).

#### 4.3.1 Cervical HPV infections

- **Incident cervical HPV infection:** an incident cervical infection with a given HPV type is defined as the new detection of this HPV type (by PCR) at any time point during the follow-up period (i.e. after enrolment in the control arm of study HPV-008).
- **Transient cervical HPV infection:** a transient cervical infection with a given HPV type is defined as the detection of this HPV type (by PCR) at any single time point during the follow-up period followed by a negative sample for that HPV type at the evaluation performed 6 months after the evaluation when the cervical HPV infection was first detected.
- **6-month persistent cervical HPV infection:** a persistent cervical HPV infection (6-month definition) is defined as the detection of the same HPV type (by PCR) in cervical samples at two consecutive evaluations over approximately a 6-month interval. Thus, the algorithmic definition of a 6-month persistent infection is that there exists a sequence of positive samples with the same HPV type, not interrupted by negative samples, such that the total range is more than 5 months ( $> 150$  days). The start of the persistent cervical HPV infection is defined as the date of the first positive sample in the sequence.
- **12-month persistent cervical HPV infection:** a persistent cervical HPV infection (12-month definition) is defined as the detection of the same HPV type (by PCR) at all available time points over approximately a 12-month interval. Thus, the algorithmic definition of a 12-month persistent cervical infection is that there exists a sequence of positive samples with the same HPV type, not interrupted by negative samples, such that the total range is more than 10 months ( $> 300$  days). The start of the persistent cervical HPV infection is defined as the date of the first positive sample in the sequence.
- **Other cervical HPV infection:** other cervical HPV infections than those described above will be considered in the analysis. These infections are cervical HPV infections with duration less than 150 days and cervical HPV infections detected at the last visit and for which it is not possible to determine if they are transient or persistent.

- **Clearance of cervical HPV infection:** two definitions will be used:
  - *Definition 1:* the clearance of an cervical HPV infection, whether incident, transient or persistent, with a given HPV type is defined as the occurrence of at least **a negative sample** for HPV DNA (by PCR) of that HPV type at the evaluation performed 6 months after the evaluation when the incident or transient cervical HPV infection was detected or when the last positive sample of the 6-month or 12-month persistent cervical HPV infection was detected.
  - *Definition 2:* the clearance of an cervical HPV infection, whether incident, transient or persistent, with a given HPV type is defined as the occurrence of at least **two negative samples** for HPV DNA (by PCR) of that HPV type at the evaluation performed 6 month after the evaluation when the incident or transient cervical HPV infection was detected or when the last positive sample of the 6-month or 12-month persistent cervical HPV infection was detected.

The flowchart in Section 8.2 provides an example of the determination of cervical HPV infection endpoints for a given HPV type.

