### 4.4.2 Clinical determinants

For each reference cervical HPV infection with a given HPV type over the 48-month follow-period, the following determinants will be defined:

- HPV type: 16; 18; 31; 33; 45; Other high risk HPV type; Other low risk HPV type.

The above categorization of HPV types will be used in the univariate and multivariable analyses. All HPV types will be considered individually in the tables presenting descriptive statistics by HPV type as well as high risk and low risk categories. The high risk (oncogenic) category is obtained by grouping together HPV types 16, 18, 31, 33, 35, 39, 45, 51, 52, 56, 58, 59, 66, and 68. The low risk (non-oncogenic) category is obtained by grouping together HPV types 6, 11, 34, 40, 42, 43, 44, 53, 54, 70 and 74. In some cases, the category “No cervical HPV infection” will be added in the categorization for univariate and multivariable analyses.

- HPV infection category: 6-month persistent, less than 6-month persistent, transient, last visit detected.
- Previous cervical HPV infection: No; Yes, with at least one high risk HPV type; Yes, with only low risk HPV type.
- Histopathologically-confirmed CIN2+ (or CIN1+, or CIN3+) following the reference cervical HPV infection, associated with a different HPV type, and preceding the CIN2+ (or CIN1+, or CIN3+) associated with the same HPV type as the reference infection (i.e. date of CIN2+ (or CIN1+, or CIN3+) following the reference infection strictly inferior to date of CIN2+ (or CIN1+, or CIN3+) associated with the same HPV type as the reference infection): No; Yes, with at least one high risk HPV type; Yes, with only low risk HPV type.

- Histopathologically-confirmed CIN2+ (or CIN1+, or CIN3+) preceding the reference cervical HPV infection, associated with a different HPV type : No; Yes, with at least one high risk HPV type; Yes, with only low risk HPV type.
- Co-infection with other HPV types (concomitant cervical HPV infections): No; Yes, with at least one high risk HPV type; Yes, with only low risk HPV type.

Co-infection with other HPV types is defined as the detection of these HPV types at time of the onset of the reference cervical HPV infection or, if this infection is persistent, during the duration of the reference cervical HPV infection until its end or until the occurrence of the event, whichever comes first.

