## **6.2.4 Analysis of time between persistent cervical HPV infections and lesions**

### **6.2.4.1 Population**

The population for the analysis of time between confirmed persistent cervical HPV infections (6-month definition) and histopathologically-confirmed CIN2+ (or CIN1+, or CIN3+) associated with the same HPV type will be restricted to subjects from the TVC-1-Control arm cohort for whom at least one 6-month persistent cervical HPV infection was detected so that a starting date is available for the computation of the time between persistent infections and lesions.

Subjects with positive or missing HPV DNA at Month 0 for the HPV type associated with the endpoint will be taken into account in the analysis as well as subjects for whom a histopathologically-confirmed CIN2+ (or CIN1+, or CIN3+) associated with a given HPV type is detected prior to the detection of the first 6-month persistent cervical infection of that HPV type (see Sections 6.2.4.3 and 6.2.4.4 for handling this particular case).

The cervical HPV infections of subjects positive for HPV DNA at Month 0 and negative for HPV DNA at Month 6 (for the HPV type associated with the endpoint) will be considered as transient cervical HPV infections. As a matter of fact, such cervical HPV infections may be either transient or persistent but the start date of infections which started before study entry is unknown. Consequently, these infections will not be taken into account in the analyses.

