#### **6.2.6.4 Statistical methods**

The clearance of cervical HPV infections (two definitions) will be analyzed using marginal binary-response models such as generalized estimating equation (GEE) regression models for clustered binary responses [Zeger et al., 1988].

These multivariable analyses will allow taking into account that women may contribute to several observations related to different HPV types, resulting in multiple event times, in addition to estimating the simultaneous effects of determinants. The GEE approach will adjust for the dependency caused by the repeated observations on the same subject by estimating robust standard errors for parameter estimates. The appropriate correlation matrix structure accounting for within-subject correlation will be determined at the time of the statistical analysis based on the patterns observed.

Interactions between determinants of interest and the type of cervical HPV infection will be explored by introducing interaction terms between these determinants and a variable categorizing the type of cervical HPV infections as transient or other, 6-month persistent and 12-month persistent (See Sections 4.4.2 and 4.4.3 for the definition of behavioral and clinical determinants and Section 8.5.2 for the list of determinants that will be taken into account in the analysis). In the presence of strong interactions, the analyses will be stratified according to the type of cervical HPV infection.

Results from the multivariable regression models will include odds ratios (95% CI).

Depending on the results, other models taking into account the time between cervical HPV infections and their clearance (i.e. Cox regression models) may be used also as described in Section 6.4.2.5. In such case, cervical HPV infection detected at the last visit will be excluded of the analysis because they will all be censored at day 0.

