|                     | Intra-uterine device                                                                                                                                                                                                                              | Binary | No
Yes                                                                              | No             | Re-assessed at each visit |
|                     | Sterilized                                                                                                                                                                                                                                        | Binary | No
Yes                                                                              | No             | Re-assessed at each visit |
|                     | Chlamydia trachomatis                                                                                                                                                                                                                      | Binary | No
Yes                                                                              | No             | Re-assessed at each visit |
| Clinical covariates | HPV infection category §                                                                                                                                                                                                                          | Class  | 6-month persistent
Less than 6-month persistent
Transient
Last visit detected | No             |                           |
|                     | Previous cervical HPV infection                                                                                                                                                                                                            | Class  | No
Yes, with at least one high risk HPV type
Yes, with only low risk HPV type    | No             | Re-assessed at each visit |
|                     | Histopathologically-confirmed CIN1+ following the reference cervical HPV infection, associated with a different HPV type, and preceding the CIN2+ (or CIN1+, or CIN3+) associated with the same HPV type as the reference infection | Class  | No
Yes, with at least one high risk HPV type
Yes, with only low risk HPV type    | Yes            | Re-assessed at each visit |

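### Infection class depends on samples taken after the first positive, yet it acts from that first positive: as a fixed covariate in the any-infection Cox models and as the entry rule in the persistent-infection analyses

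*SAP*

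**What the plan says.** SAP 4.3.1 calls an infection 6-month persistent when there is a run of positives "not interrupted by negative samples, such that the total range is more than 5 months" (more than 150 days). It calls an infection transient when the first positive is "followed by a negative sample for that HPV type at the evaluation performed 6 months after the evaluation" at which the type was first found. An infection first seen at the last visit is one that cannot be resolved either way. Each class therefore needs later samples, or their absence. The clock does not wait for them: "The start of the persistent cervical HPV infection is defined as the date of the first positive sample in the sequence".

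The class is then used in two places.

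- **Persistent-infection analyses (6.2.4, CIN2+ primary).** The population is restricted to subjects "for whom at least one 6-month persistent cervical HPV infection was detected so that a starting date is available" (6.2.4.1). Time is event or censoring date minus detection date of that infection (6.2.4.4).
- **Any-infection analyses (6.2.5, secondary).** 4.4.2 defines the determinant as "HPV infection category: 6-month persistent, less than 6-month persistent, transient, last visit detected". The table in 9.5.1 includes it, with the level "Last visit detected", marks it not time-dependent, and by footnote limits it to the any-infection analyses.

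For the optional Cox model of clearance, 6.2.6.4 says that "cervical HPV infection detected at the last visit will be excluded of the analysis because they will all be censored at day 0". The lesion models carry no such exclusion.

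**The concern.** A Cox model compares infections at each moment using what is known at that moment. Here the label persistent is applied from day 0 although it is earned at least 150 days later. If a lesion, its treatment, or dropout linked to it prevents the confirming positive, that lesion leaves the persistent class and, when a later sample is negative, is counted as transient. The early part of the curve and the persistent-versus-transient hazard ratio would then partly reflect the classification rule and not biology. Time from onset of persistent infection to CIN2+ is the primary objective, so the early part of the curve matters.

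The last-visit level raises a separate problem: it is a covariate level with next to no follow-up behind it.

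**Working it through.** **1. Which clock does the SAP use?** The worked examples in 9.4.1 settle it. The shown months are subtracted below. The annex table has no Month 18 column, so the second positive of #3 is taken as shown.

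| Subject | First positive | Second positive | End | Stated time | From first positive | From second positive | Share before class is known |
|---|---|---|---|---|---|---|---|
| #1 | M6 | M12 | M30 (CIN3) | 24 | 30 − 6 = 24 | 30 − 12 = 18 | 6/24 = 25% |
| #3 | M12 | M24 | M48 (censored) | 36 | 48 − 12 = 36 | 48 − 24 = 24 | 12/36 = 33% |
| #4 | M24 | M30 | M48 (censored) | 24 | 48 − 24 = 24 | 48 − 30 = 18 | 6/24 = 25% |

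Subject #2 in 9.4.2 agrees: 48 − 6 = 42, as stated. The clock starts at the first positive, and a quarter to a third of the credited time comes before the class is known.

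**2. How large could the effect be?** Only the PCR schedule comes from the SAP (3.2: Months 0, 6, 12, 18, 24, 30, 36, 48). The rest is assumed:

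- 400,000 infections with onset spread evenly over the visits M0 to M36;
- constant lesion hazard of 0.03 or 0.10 per year, the same in both classes (true hazard ratio 1);
- probability 0.5 that the next sample is positive;
- 5% lost before the next sample, independently of lesions;
- a share q of lesions found before the next sample is treated and the type then tests negative.

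The 12-month look-back and the rule assigning events first to persistent infections were not simulated. Cox models were fitted to random subsets of up to 150,000 infections.

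| q | HR persistent vs transient, 0.03/yr | HR, 0.10/yr |
|---|---|---|
| 0 | 0.99 | 0.98 |
| 0.25 | 0.89 | 0.86 |
| 0.5 | 0.79 | 0.76 |
| 0.75 | 0.70 | 0.67 |
| 1 | 0.62 | 0.59 |

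At 0.05 per year and q = 1, the ratio is 0.69 if the chance of a positive next sample is 0.3 and 0.49 if it is 0.7. A landmark at the next sample gives 0.97 to 1.01 in every scenario.

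**3. The persistent-only risk set.** With early risk e = 1 − exp(−0.03 × 0.5) = 1.49%, the six-month risk left in the persistent set is (1 − q)e / (1 − qe). For q = 0.5 this is 0.00744 / 0.99256 = 0.75%, and for q = 1 it is 0. The simulation agrees (0.8% and 0.0%). At 0.10 per year the simulated 12-month risk is 9.5%, 7.2% and 4.9% for q = 0, 0.5 and 1 (truth 9.5%). The 24-month risk is 18.0%, 16.0% and 13.8% (truth 18.1%).

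**4. The last-visit level.** Under 6.2.5.4 a subject who attended all visits is censored at the Month 48 visit. An infection first seen there has 48 − 48 = 0 months at risk. For incomplete attenders, time beyond the last PCR arises only if a cytology or biopsy follows it. Events in this level therefore come largely from the rule that sets a lesion in the preceding 12 months to time 0, or from cytology or biopsy after the last PCR.

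**The case against.** Several stronger readings are tempting, and the SAP does not support them.

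- **An early treated lesion can never enter the primary analysis.** Not so. A lesion between the two positives counts if the type stays positive, and 6.2.4.3 and 6.2.4.4 count a lesion up to 12 months before a persistent infection as an event at time 0.
- **Early risk is necessarily understated.** Not shown. The look-back, and the rule in 6.2.5.3 that gives an event first to a persistent infection, push risk in the persistent class up. With q = 0 and independent loss the simulation shows no bias. SAP 4.3.2 mentions excision specimens but gives no share treated.
- **The simulated sizes are estimates for this study.** They are not. Hazards and q are assumptions, and 3.2 schedules routine cytology yearly, so a constant detection hazard is a simplification.
- **The last-visit level cannot be estimated at all.** Too strong. Later cytology or biopsy can add time and events, and 6.1.2 allows sparse categories to be regrouped. Sparse and unstable is the fair description.
- **The hazard ratio for other-type CIN is infinite.** 4.4.2 requires the date of the other-type CIN "following the reference infection strictly inferior to date of CIN2+ (or CIN1+, or CIN3+) associated with the same HPV type as the reference infection", a date that does not exist for infections without the event. But 9.5.1 marks this covariate time-dependent and re-assessed at each visit. The infinite ratio follows only from coding 4.4.2 literally.
- **Delayed entry should replace the primary analysis.** It would leave nobody at risk in the first 150 days and drop lesions dated before confirmation, so it cannot describe time from onset.

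It might also be said that 6.2.4.5 already allows a counting process. It does, but for repeated observations per subject. No landmark or delayed entry is specified.

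**Conclusion.** The point stands in bounded form. A class known only later is treated as known at the first positive. This applies to the fixed covariate of the secondary any-infection models and, separately, to selection of the risk set in 6.2.4. Net direction and size are unknown. Loss of early lesions from the persistent class pulls one way; the look-back and the persistent-first assignment pull the other, and themselves use later information. For the first mechanism alone, at 3% per year, even odds of a positive next sample and a true ratio of 1, the hazard ratio lies between 0.99 and 0.62 depending on a treated share that the SAP does not give.

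The last-visit problem needs no simulation. The SAP recognises day-0 censoring for clearance and leaves the same infections in the lesion models. The change is worth making: section 7 shows the primary result already delivered for a poster, but the full results for the manuscript still to come.

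**What to change.** 1. **6.2.5 and 9.5.1:** make infection category time-dependent, switching to the 6-month persistent level at the positive sample that takes the run beyond 150 days. A landmark at the next sample is the alternative. Exclude last-visit infections from the lesion Cox models, as 6.2.6.4 does for clearance, and report how many infections and events this removes.
2. **6.2.4:** keep the present analysis, with onset as origin, as the description of time from onset. Add a delayed-entry or landmark Cox analysis from the confirming positive for the determinant effects.
3. **4.4.2:** align the wording for other-type CIN with 9.5.1, so that the indicator switches on at its own date for every infection, with or without the event.

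The cost is SAP wording and a start-stop data set, compatible with the counting process named in 6.2.4.5. The price of the added 6.2.4 analysis is that lesions dated before confirmation and the time-0 events do not count in it, and it says nothing about the first 150 days. That is why it supplements the onset-based analysis and does not replace it.
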